| **Statistical Considerations** | Sample size: in order to have a significant difference between tracheal and esophageal groups, with a power of 90% and a significance level of 0.01 (one-tailed z test), and anticipating a 10% in the registration failure rate, we plan to enroll 40 patients for group A. In order to have a significant difference between esophageal and gastric pH value, with a power of 90% and a significance level of 0.01 (one-tailed z test), and anticipating a 10% of drop off rate, we plan to enroll 35 patients for group B.  Primary analysis: The adherence to the protocol is checked for each enrolled patient during the study. We assess and report total adherence rate to our protocol in order to analyse data on the intention-to-treat (ITT) and on the per-protocol (PP) population. We test the hypothesis of difference in the proportion of etCO2 level into the tracheal group and into the esophageal group (measurements collect in patients enrolled in group A), with the ITT. We execute a z-test for comparison of the two proportions. The null hypothesis of no difference between the two proportions is not accept if the p-value is 0.01. Similarly, in group B patients is test the hypothesis of difference in the proportion of pH level into the esophageal group and into the gastric group, with the ITT. We carry out a z-test for comparison of the two proportions. The null hypothesis of no difference between the two proportions is not accept if the p-value is 0.01. |
| **Risk / Benefit Assessment** | This study consists in parameters collection in patients who required a NGT positioning. Any potential clinical risk is related only to the standard procedure of NGT placing.  There will be no immediate benefits to the enrolled patients. Future patients who required a NGT positioning could benefit due to the potential of using threshold values as predictors of correct NGT placing, offering better treatment approach which not required thoraco-abdominal anterior-posterior radiography as diagnostic gold standard. |

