# Study OBJECTIVES and Design

## 4.1 Primary and secondary endpoints

The primary endpoint is to identify the threshold value in the distribution and in the frequency of etCO2 and pH values. The pH values will be compared with the performed X .

The threshold values for etCO2 and for pH will be determined in two groups: group A, with the aim to find a threshold value of etCO2 above which we can be sure that aspiration probe is in the trachea and group B, with the aim to find a threshold value of pH below which we can be certain that NGT is in the stomach.

Further secondary results are expected:

- for patients in group A it will be necessary to perform a sub-analysis for the threshold value in the group of patients suffering from COPD;

- for patients in group B, a sub-group analysis will be performed for the threshold value for patients taking proton pump inhibitors (PPIs), and / or in the presence of an already diagnosed gastro-esophageal reflux disease.

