## 6.2. Statistical analysis plan

We tabulate the distribution of baseline variables across the study sections, summarizing categorical variables by frequencies and percentage and numerical variables either by mean and standard deviations (±SDs), or by medians and interquartile ranges (IQR). Data distribution was verified using a Kolmogorov- Smirnov test.

We checked adherence to the protocol for each patient during the study. We assess and report total adherence rate to our protocol in order to analyse data on the intention-to-treat (ITT) and on the per-protocol (PP) population. Primary analysis is carried out on the ITT population for each study group, irrespective of potential non-adherence to the study protocol. Secondary analyses included analysis on the PP population, concerning the patients enrolled and treated following all the study procedures. The results of the performed analyses on the two populations are compared. All hypothesis tests are one-sided and considered significant if p-value is ≤ 0.01. Analyses are accomplished with the intention-to-treat if not otherwise specified.

In group A we tested the hypothesis of difference in the proportion of etCO2 level into the tracheal group and into the esophageal group (measurements collected in patients enrolled in group A), with the ITT. We executed a z-test for comparison of the two proportions, refusing the null hypothesis of no difference between the two if the p-value was ≤0.01. This to identify the threshold value of etCO2 above which tracheal location of NGT is determined with high precision. Similarly, in group B we tested the hypothesis of difference in the proportion of pH level into the esophageal and gastric group, with the ITT. We carried out a z-test for comparison of the two proportions, refusing the null hypothesis of no difference between the two if the p-value was ≤ 0.01. This to identify the threshold value of pH below which gastric location of NGT is determined with high precision. Statistical analysis was performed using SPSS version 10.0 (IBM, Chicago, IL, USA) for Mac OS.

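### The planned z-test of two proportions cannot identify the etCO2 or pH threshold that is the primary endpoint, gives no error rate for one, and ignores the pairing of the readings

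*Protocol*

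**What the plan says.** Protocol section 4.1 defines the target: "The primary endpoint is to identify the threshold value in the distribution and in the frequency of etCO2 and pH values". It sets a demanding standard for both markers. In group A the aim is to "find a threshold value of etCO2 above which we can be sure that aspiration probe is in the trachea"; in group B it is to "find a threshold value of pH below which we can be certain that NGT is in the stomach".

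Section 6.2 gives one primary analysis per group, on the intention-to-treat population, one-sided at 0.01. For group A: "We executed a z-test for comparison of the two proportions, refusing the null hypothesis of no difference between the two". The purpose is stated directly afterwards: "This to identify the threshold value of etCO2 above which tracheal location of NGT is determined with high precision". Group B has the same test and a parallel purpose: "This to identify the threshold value of pH below which gastric location of NGT is determined with high precision". The synopsis (Statistical Considerations) repeats the test: "We execute a z-test for comparison of the two proportions".

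Section 4.3 says that each patient contributes two readings, one per site, and for group B it points to Section 6 for the analysis that will produce the threshold. Section 6 contains only the z-test.

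**The concern.** etCO2 and pH are numerical readings. They become proportions only after a cut-off has been applied, and the protocol names none for this purpose and gives no rule for choosing one. The test therefore presupposes the quantity it is meant to deliver. Its p-value says whether two proportions differ. It does not say where the cut should lie or how often a reading at the wrong site would fall on the wrong side of it.

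The two-proportion z-test also assumes independent samples, whereas the tracheal and oesophageal readings (or oesophageal and gastric) come from the same patient.

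At stake is the use the protocol foresees. The synopsis and section 8.2 present the thresholds as possible predictors of correct placement that could make radiography unnecessary. A threshold meant for that purpose needs a stated error rate, and the planned analysis yields none.

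**Working it through.** **Inputs.** Section 6.1: 35 and 30 evaluable patients, 10% loss, 40 and 35 enrolled. Section 6.2: one-sided 0.01. Expected values: trachea 40 mmHg (range 35-45 in sections 3.1 and 4.3; CI 30-50 in section 6.1), oesophagus <25 mmHg; gastric pH 3.8 (3.2-4.4); oesophageal pH 8.5 (6-9.5) in sections 3.1 and 4.3, but about 7 (5-8) in section 6.1.

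**The plan's own figures.** The loss allowance reproduces approximately: 35/0.9 = 38.9, so 39 (40 planned); 30/0.9 = 33.3, so 34 (35 planned). The 35 and 30 cannot be derived, because the two proportions that the test compares are not given. Evaluable pairs used below: 40 × 0.9 = 36, and 35 × 0.9 = 31.5, taken as 31.

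**Step 1: what the criterion permits.** With n pairs, a correct-site and b wrong-site readings on the positive side of a cut, and p̄ = (a + b)/(2n):

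z = [(a − b)/n] / √[p̄(1 − p̄) · 2/n]; specificity = (n − b)/n.

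- Group A, 36/36 vs 30/36: p̄ = 66/72 = 0.9167; z = 0.1667/0.0651 = 2.56; one-sided p = 0.0053. Specificity 6/36 = 17% (exact 95% CI 6% to 33%).
- Group B, 31/31 vs 26/31: p̄ = 57/62 = 0.9194; z = 0.1613/0.0692 = 2.33; one-sided p = 0.0098. Specificity 5/31 = 16%.

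**Step 2: the pairing.** When every discordant pair points the same way, the exact one-sided McNemar p is 0.5^d for d discordant pairs.

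- Group A example, d = 6: p = 0.016. Group B example, d = 5: p = 0.031. Neither passes 0.01, so these two tables depend on the unpaired form.
- With d = 7, p = 0.008, which passes. Specificity is then 7/36 = 19% or 7/31 = 23%.

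A paired test moves the limit a little; it does not turn a p-value into a threshold.

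**Step 3: does significance point to one cut?** Assumptions: normal readings; SD 5.1 mmHg at both sites (30-50 read as a 95% range, 20/3.92); n = 36. The oesophageal mean is not stated, so a range is shown.

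| Oesophageal mean | Cuts whose expected proportions pass at 0.01 |
| --- | --- |
| 25 mmHg | about 19.5 to 45.5 mmHg |
| 10 mmHg | about 4.5 to 45.5 mmHg |

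For pH (gastric 3.8, SD 0.31; oesophageal 7, SD 0.77; n = 30), every cut from about 3.5 to 7.7 passes.

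**Step 4: what the planned numbers can support.** With zero false positives in n wrong-site readings, the one-sided 95% upper bound is 1 − 0.05^(1/n):

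- n = 36: 8.0%.
- n = 31: 9.2%.

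Putting the lower bound for specificity at 95%, 98% or 99% with zero errors takes 59, 149 or 299 wrong-site readings (n ≥ ln 0.05 / ln specificity). A cut placed at the most extreme of n wrong-site readings shows no errors in the sample, but its expected error in a new patient is 1/(n + 1): 1/37 = 2.7% or 1/32 = 3.1% (continuous readings assumed).

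**The case against.** The strongest defence is that details of threshold selection belong in a statistical analysis plan that is not shown. It would hold if section 6.2 were silent. It is not: it says that the z-test is what identifies the threshold, and section 4.3 sends the reader to Section 6 for it. An analysis plan that followed the protocol would inherit the error.

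Other objections limit how far the point goes, and they stand.

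- A reader might infer that the trial is likely to adopt a cut with 17% specificity. The documents do not support that. The expected ranges do not overlap (35-45 vs <25 mmHg; pH 3.2-4.4 vs 6-9.5, or vs 5-8), and the stated aim is high precision.
- A reader might infer that no threshold can come out of this trial. That is too strong. Section 4.1 looks for it in the distribution of the values, and both sets of readings are collected. What is missing is a rule and an error rate.
- A reader might stress false-positive inflation from searching over cuts: about 11 to 13% instead of 1% for independent readings, about 5 to 7% at a latent correlation of 0.5. Those figures assume no true difference between sites, which the protocol's own expected values make implausible. The optimism that matters is in the estimated accuracy.
- A reader might take 25 mmHg as a cut-off the protocol already quotes. Section 3.1 gives it only as a bound on the expected oesophageal value, and section 3.2 says that no study has established an etCO2 threshold. Only pH <5.5 is reported as a cut-off.

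**Conclusion.** The point holds and should be corrected before analysis. The stated primary analysis does not produce the primary endpoint, attaches no sensitivity or specificity to it, and has the wrong form for paired readings. The criterion admits cuts with about 16-17% specificity in the unpaired form, or about 19-23% under an exact paired test, and is met across a wide band of cuts. Because the sites are expected to differ strongly, the practical consequence is a test that almost surely passes and leaves the threshold question open.

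The tables in steps 1 and 2 rest only on 10% loss from the planned enrolment. The bands in step 3 also rest on normality and on SDs read from the quoted ranges, and for etCO2 on assumed oesophageal means. That 35 and 30 could not be reproduced reflects the missing proportions and does not show that those numbers are wrong. Separately, the planned numbers cannot support certainty: with no errors at all, a false-positive rate of about 8% or 9% is not excluded.

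**What to change.** Replace the z-test as primary analysis in section 6.2 and the synopsis:

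- For each marker, estimate the ROC curve (trachea vs oesophagus for etCO2; stomach vs oesophagus for pH).
- Choose the cut-off by a rule fixed in advance, with a stated specificity target.
- Report sensitivity and specificity at that cut with exact confidence intervals.
- Correct for choosing and judging the cut on the same readings by resampling patients, keeping each pair together. If a bootstrap interval for the cut-off itself is given, add the caveat that it is unreliable when the cut lies near the most extreme reading.
- Also report accuracy at pH 5.5, which needs no selection from the data. Accuracy at 25 mmHg is optional and should be labelled as the quoted upper bound of expected oesophageal etCO2, not as an established cut-off.
- If a test of site difference is kept, make it paired and secondary.
- Word the conclusion as an estimated threshold with its error bound, and align the wording on certainty in section 4.1 with the 8% and 9% limits.

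Cost: rewording and a little more analysis. The paired readings are already collected, so no further patients or measurements are needed for this. Reported accuracy will be less favourable after correction. A much tighter bound on specificity would need more wrong-site readings than are planned.

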# 7 Regulatory Aspects AND SAFETY

## 7.1 Local regulations / Declaration of Helsinki

This research project will be conducted in accordance with the protocol, the Declaration of Helsinki, the principles of Good Clinical Practice, the Human Research Act (HRA) and the Human Research Ordinance (HRO) as well as other locally relevant regulations.

## 7.2 Serious Events

If a serious event occurs, the research project will be interrupted and the Ethics Committee notified on the circumstances via BASEC within 7 days according to HRO Art. 21.

## 7.3 Amendments

Substantial changes to the project set-up, the protocol and relevant project documents will be submitted to the Ethics Committee for approval according to HRO Art. 18 before implementation. Exceptions are measures that have to be taken immediately in order to protect the participants.

## 7.4 End of the project

Upon project termination, the Ethics Committee is notified within 90 days. See Section 9.4 for further details on how health-related data will be handled upon termination of the project.

## 7.5 Insurance

The research project is of category A according to HRO Art. 7. No insurance would be required for this study.

# 8 FURTHER Aspects

## 8.1 Overall ethical considerations

The Project Leader affirms and upholds the principle of the participants’ right to dignity, privacy and health and that the project team shall comply with applicable privacy laws. Especially, anonymity of the participants shall be guaranteed when presenting the data at scientific meetings or publishing them in scientific journals.

Individual participant medical information obtained as a result of this research project is considered confidential and disclosure to third parties is prohibited. Participant confidentiality will be further ensured by utilizing identification code numbers to correspond to medical information in the computer files.

For data verification purposes, a competent authority or an ethics committee may require direct access to parts of the medical records relevant to the project, including participants’ medical history.

## 8.2 Risk-benefit assessment

This study consists in several parameters collection in patients who required a NGT positioning. Thus, any potential clinical risk is related only to the standard procedure of NGT placing.

There will be no immediate benefits to the enrolled patients. Future patients who required a NGT positioning could benefit due to the potential of using threshold values as predictors of correct NGT placing, offering better treatment approach which not required thoracic-abdominal anterior-posterior radiography as diagnostic gold standard.

# 9 Quality CONTROL AND Data protection

## 9.1 Quality measures

The project will be conducted according to the ICH-GCP and national requirements. Quality assurance and control will follow the Project Leader’s SOPs.

The Project Leader is responsible for proper training of all personnel delegated to perform study-related activities and for supervising the conduct of the study.

All collected data will be double-checked by the Project Leader or delegated person, different from the one who entered the data, to ensure accuracy and consistency; correction will be done accordingly.

## 9.2 Data recording and source data

The physicians will maintain individual records of each patient. These records constitute source data. Case Report Form (CRF) specifically created for this study will be used to collect clinical data. The CRFs have to be completed in a timely manner. All source data will be kept according to all applicable regulatory requirements.

Only coded data will be entered in the CRF and these will be stored at the Clinical Research Unit of Clinica Luganese Moncucco. The access is restricted only to authorized staff. A patient identification list must be maintained in order to allow identification of a patient. Coding keys is stored at the project leader site. Only persons involved in the study will have access to the key.

## 9.3 Confidentiality and coding

Study and participant data will be handled with uttermost discretion and is only accessible to authorized personnel who require the data to fulfil their duties within the scope of the study. On all project specific documents, participants are only identified by a unique participant number.

## 9.4 Retention and destruction of study data and biological material

All project data and relevant source documents will be maintained at the Project’s leader site for a minimum of 10 years after study termination or premature termination of the project.

# 10. Funding / Publication / declaration of Interest

We will expect a financial support of around 3500 CHF from Nestlé. The confirmation will be given in the next few weeks (mid-December).

The Project Leader has the responsibility of the collected data.

In case of a project grant, the company will have none property on the collected data.

The Project Leader and all investigators involved into the study have no conflict of interest to declare.

The projects results are planned to be reported in an original article to be submitted to a peer reviewed scientific journal.

| **Medical history** |  | + |  |
| **Participant characteristics** |  | + |  |
| **Procedures** |  |  | + |
| **Sampling** |  |  | + |
| **Safety** |  | + | + |
